### **Substance specific patient centered outcomes.**

**Problems and consequences associated with alcohol and marijuana use:** Standard measures of consequences related to substance use typically mix all substances together, creating a composite scale. For this project, we will separately determine the most common consequences reported by adolescents associated with alcohol use and marijuana use. Using the Personal Experience Screening Questionnaire (PESQ), we will ask participants substance specific outcome questions to determine whether alcohol and marijuana have different patterns of outcomes.

**Sexual risk associated with substance use:** Risky sexual contact is commonly associated with alcohol use. Using questions adapted from the Youth Risk Behavior Survey, we will assess if a participant has ever engaged in sexual contact. Specifically we are interested in whether there are different relationships and perceived concerns between alcohol and/or marijuana and unprotected sex.

### **Disease specific health questions**

**Disease management:** We will ask a set of questions to learn more about current disease status and how patients manage their chronic medical conditions. Diabetes specific questions include use of an insulin pump, use of a glucose monitor, number of times he/she has had their hemoglobin A1c (HbA1c) checked by a doctor in the past 12 months, last HbA1c reading, and number of times they check their blood sugar daily. Rheumatologic condition specific questions include a pain scale and how often they have experienced morning stiffness in the past 30 days.

**Disease severity:** We will ask patients with type 1 diabetes about episodes of severe hyperglycemia and hypoglycemia and patients with rheumatological conditions about frequency of disease flares to learn more about their medical condition.

**Intervention:**

Those in the intervention arm will receive a computerized brief intervention composed of tailored feedback and psycho-education. Content in the intervention will focus on health promotion and will deliver positive messages about health.

The Co-PIs previously conducted a qualitative study (Validating NIAAA's Brief Screening Guide in Youth with Chronic Medical Conditions) among YCMC receiving care at BCH. The goal of the study was to understand how they navigate their chronic medical condition in general and in social situations, situations in which they have used or not used substances, and the quality of messages they have received about their health. The core domains this intervention will focus on were adapted from data collected during the qualitative study and a literature review on the topic. The domains were refined and then pilot tested with a sample of patients who participated in the aforementioned qualitative study.

Domains included in the intervention are 1) disclosure of disease to peers and resistance skills; 2) adolescent development; 3) medication adherence; 4) and disease specific knowledge. The topic area will include information on science or key findings in research, narratives from peers on their experiences, and actionable items or key messages that reinforce the topic. Quotes from youth with chronic medical conditions collected from the previous qualitative study were included as part of the narrative sections to provide participants with messages from peers.

**Disclosure of disease to peers and resistance skills:** Studies have shown that peer support from close friends had an impact on stressors such as adjusting to a chronic condition or coping with a difficult medical treatment in youth with chronic medical conditions. We are also interested in including a section on refusal skills in our intervention. Findings suggest that resistance skills training may be especially effective before the onset of behavior as a primary prevention tool. Youth who lack refusal skills are more likely to engage in alcohol use in early adolescence and this trend persists into later adolescence as well. These two themes will be combined into a section about encouraging communication with peers if they have not already done so and increasing comfort in doing so. It also includes recommendations to use close friends in building resistance skills, having "sober buddies" and in supporting decisions not to use substances.

**Adolescent Development:** Adolescents growing up with a chronic medical condition face unique challenges and burdens compared to other adolescents. Findings from our qualitative study showed that many adolescents felt their condition and management of their health made them feel more responsible and mature compared to others their age. This section will focus on acknowledging that while YCMC may feel burdened by their condition there may be positive ways in which their condition has changed their life, including increased maturity and resilience.

**Medication Adherence:** A previous study by the Co-PIs found that high school youth who reported past year alcohol use were 1.79 times as likely to report they forgot to take their medications and 1.61 times as likely to report skipping their medications "always/ often/sometimes" over the past 30 days than youth who did not report past year alcohol use. This section will provide information around medication adherence and the possible effects of substance use on adherence.

**Disease Knowledge:** A previous study by the Co-PIs also showed that knowledge about whether alcohol can interfere with medications or laboratory tests used to treat chronic conditions was low among YCMC. Alcohol use among youth with type 1 diabetes can pose serious health risks such as hypoglycemia. A common theme in the qualitative work by the Co-PIs was a preference from adolescents for direct and honest information about the disease-specific risks of substance use without “any gray areas” or “sugarcoating” information. The knowledge section will focus on presenting information about how alcohol is processed in the body and how this may impact chronic conditions or the effectiveness of the medications used to treat chronic conditions.

**Control:** Those in the control arm will receive information/brief advice around internet safety. Information for the internet safety was adapted from existing curriculum available through Netsmartz and KidsHealth.org. The core topic around internet safety will focus on how youth can protect their online presence and increase awareness of their “digital footprint”. We will provide information on the importance of being safe about posting online, possible consequences of what posting personal information, and protecting online privacy.

**Follow-up Assessment:** We will follow up with the recruited sample 6 months and 12 months post baseline. We will administer an abbreviated Assessment Battery, either online or via phone, with a focus on changes in behavior since baseline to measure substance use and outcome trajectories over time. The assessment batteries administered at 6 and twelve months post baseline are attached to this protocol.

### **Parent Assessment Battery**

We will recruit parents of participants enrolled in the trial to complete an assessment battery at baseline. We will ask parents questions to ascertain their opinions around a variety of health related issues and how they relate to their child with a chronic condition. Topics will include disease burden, mental health, care transition, knowledge and attitudes around substance use, social media use, and use of marijuana as medicine. Due to the lack of studies that have looked specifically at parents of youth with chronic medical conditions and many of these topics, a number of our questions are novel, however questions in this survey have been pilot tested and well received in a related anonymous survey of parents whose children have chronic medical conditions (IRB-P00017232).

## **2.3 Eligibility Criteria for Selection of Study Population**

### **2.3.1 Inclusion Criteria (Reference: Protocol p. 6)**

14–17-year-old youth presenting for routine medical care in the Rheumatology clinic or Endocrinology clinic at BCH, with informed assent. To be eligible, participants in the Endocrinology clinic must have a diagnosis of type 1 diabetes for at least a year and participants in the Rheumatology clinic must have a diagnosis of a rheumatologic condition for at least a year. Eligible youth must also be between 14-17 years old at the time of enrollment and be able to read and understand English at a middle school level or greater. Participants must consent to participation in the study and consent to the 6 month and 12 month follow up assessments.

Parents whose children enrolled in the study, and who are able to read and understand English at a middle school level or greater will be eligible to participate in the parent study.

### **2.3.2 Exclusion Criteria (Reference: Protocol p. 7)**

Patients who are medically or emotionally unstable or otherwise unable to provide assent at the time of their appointment as determined by their clinician or the research team, those who are unable to speak/read English at a middle school reading level, use a computer keyboard and/or complete an interviewer-assisted questionnaire will be excluded. Patients who do not consent to 6 month and 12 month re-assessment will also be excluded. Patients who are pregnant at baseline will be excluded from the study. If a participant enrolls in the study and becomes pregnant after baseline, they will not be excluded from the follow-up assessments.

Parents of enrolled participants who are not able to read and understand English at a middle school level or greater will be excluded. Parent ineligibility will not affect patient eligibility.

### **3.0 GENERAL ANALYSIS DEFINITIONS AND CONVENTIONS**

#### **3.1 Analysis Populations**

##### **3.1.1 Eligible Population (Reference: Protocol p. 7)**

The eligible population consists of all patients who have been approached for the study.

##### **3.1.2 Respondent Population (Reference: Protocol p. 7)**

The respondent population consists of all participants who have provided informed consent during the recruitment process and have been screened for eligibility.

##### **3.1.3 Intent-to-Treat Population (Reference: Protocol p. 7, p. 20)**

The Intent-to-Treat (ITT) population consists of all participants who have provided informed consent at the initiation of the screening process, have been randomized, enrolled in the study, and have responded to the survey questions.

### **4.0 PARTICIPANT ENROLLMENT AND DISPOSITION (Reference: Protocol p. 20)**

The number of respondents assessed for eligibility and participants who are enrolled, as well as those who have been included in the analytic sample, will be clarified in the CONSORT diagram. The distribution of participants' characteristics by inclusion/exclusion in the study will be assessed for any differences. Participant disposition will be summarized based on the number of participants who are retained in the study, complete the study, and the number of participants who withdrew from the study will be clarified in the CONSORT diagram.

### **5.0 ANALYSIS OF PARTICIPANT BASELINE CHARACTERISTICS (Reference: Protocol p. 20)**

To assess baseline equivalence between intervention group and control group, we will compare distribution of demographic characteristics using  $\chi^2$  test or Fisher exact test for categorical variables and t-test or Wilcoxon sign rank test for continuous variables. We will also evaluate equivalence among those lost to follow-up versus those retained by comparing demographics and outcomes among those lost and those with complete follow-up.

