This project is the second component of a two part study in which we will enroll a total of 900 adolescents as indicated by Figure 1. In this project, we will create a tailored SBIRT protocol that reflects YCMC specific concerns and risk thresholds. We will include YCMC in the general longitudinal cohort study being undertaken in the Adolescent/Young Adult Medicine clinic, and additionally enroll these youth into an embedded trial of a tailored SBIRT intervention in which we will assess acceptability and effects of the tailored SBIRT model. **For this protocol, we will be discussing the “Youth with Chronic Medical Conditions” cohort. We will enroll a total of 450 participants from the Rheumatology and Endocrinology Clinics (225 participants from each) for this study and will attempt to follow participants for one year. Accounting for attrition at 6 months and 12 months follow-up, we expect 300 participants will complete the entire study (see figure 1 for projected enrollment numbers).**

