## 748 **H. Data Analysis Plan**

749 All analyses will be conducted under the principle of intention to treat; all participants will be analyzed  
750 as members of the groups to which they were originally randomized to. To assess baseline  
751 equivalence between intervention group and control group, we will compare distribution of  
752 demographic characteristics using  $\chi^2$  test or Fisher exact test for categorical variables and t-test or  
753 Wilcoxon sign rank test for continuous variables. We will also evaluate equivalence among those lost  
754 to follow-up versus those retained by comparing demographics and outcomes among those lost and  
755 those with complete follow-up.

756 Our primary outcome variables will be initiation and escalation of substance use. Initiation of use will  
757 be defined as any new use of substances at follow-up among those reporting no past-12-month use at  
758 baseline. For alcohol use, escalation will be defined as, among drinkers, any increase in number of  
759 drinks (measured by TLFB) from baseline to follow-up. For marijuana use, escalation will be defined  
760 as, among users, any increase in days of smoking marijuana (measured by TLFB) from baseline to  
761 follow-up.

762 We will assess the magnitude and direction of the effects of hypothesized predictors on substance  
763 use. Specifically, we will examine the association between each factor and past year substance use,  
764 past 90 days use and number of drinks measured by TLFB. Multivariate logistic/linear regression,  
765 adjusting for demographic characteristics, will be performed.

766 To evaluate the effect of intervention on substance use at 6- and 12-month follow-up, we will perform  
767 multivariate logistic regression adjusting for demographics, predictors of substance use and baseline  
768 knowledge. Separate models will be used to evaluate effects at 6- and 12-month. Adjusted odds ratios  
769 will be computed for comparison between intervention and control groups.

770 We will also evaluate how well the change of intermediary measures predicts the change of  
771 substances use. We will use multiple logistic regression incorporating all intermediary variables.  
772 Separate models will be used to assess the associations at 6- and 12-month.

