## **9.0 SAMPLE SIZE AND POWER (Reference: Protocol p. 21)**

We will recruit a convenience sample of 450 adolescent patients ( $n=450$ ) and expect 300 of them will complete the entire study. With total sample size of 300 youth, there is adequate power (.80) to detect

significant effects ( $p < .05$ ) for adjusted odds ratios of  $\geq 2.0$ , defined as the likelihood that control versus intervention participants initiate or escalate their substance use behaviors from baseline to follow-up, across prevalence levels in the intervention group that range from .20 to .55.

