#### **Defining Outcomes**

Primary Outcome(s): Past 3-month alcohol use measured by a Brief Frequency variable for alcohol use.

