#### **Data Analysis Approach**

The impact of the psychoeducation program on alcohol use, measured from baseline to twelve months, taking into account correlations within individuals, using multivariate mixed-effects models adjusting for baseline characteristics.

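### SAP 5.0 and Protocol H name a paired rank test for independent arms, and with one third expected not to complete, the attrition check has no comparison by arm, undefined outcomes and no missing-data sensitivity analysis behind it

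*Supplement*

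**What the plan says.** **Baseline comparison.** SAP 5.0 compares intervention with control on continuous characteristics by "t-test or Wilcoxon sign rank test for continuous variables". Protocol H has the same test name and goes straight on to attrition: "Wilcoxon sign rank test for continuous variables. We will also evaluate equivalence among those lost". No update in SAP 11.0 changes either sentence.

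**Attrition check.** Both sections evaluate those lost against those retained by "comparing demographics and outcomes among those lost and those with complete follow-up". No time point is attached to the outcomes, and arm is not mentioned. SAP 4.0 adds participant flow counts in a CONSORT diagram and a comparison of characteristics by inclusion or exclusion, also without stating a split by arm.

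**Expected loss.** SAP 9.0 states "We will recruit a convenience sample of 450 adolescent patients" and says the investigators "expect 300 of them will complete the entire study". Protocol A spreads the loss over both visits: "Accounting for attrition at 6 months and 12 months follow-up, we expect 300 participants will complete the entire study". How it divides between 6 and 12 months is not given.

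**Outcome and model now in force.** The update of 6/27/2019 sets the primary outcome as "Past 3-month alcohol use measured by a Brief Frequency variable for alcohol use". The update of 12/16/2020 analyses alcohol use from baseline to twelve months, "taking into account correlations within individuals, using multivariate mixed-effects models adjusting for baseline characteristics". Neither document states a missing-data assumption, an imputation method or a sensitivity analysis.

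**The concern.** Two faults of different weight sit in the same paragraph.

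The first is a misnamed test. Participants in one arm are not matched to participants in the other, so there are no within-pair differences to rank. The test meant is almost certainly the rank-sum test.

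The second matters more. When a third of a sample may be lost, the reader of the trial wants to know whether the participants still observed in the two arms remain comparable. Loss can depend on substance use differently in the two arms: for instance, drinkers who have just read about the risks of alcohol may avoid a follow-up survey, while drinkers who read about internet safety do not. A lost-versus-retained comparison that ignores arm averages over such opposite patterns. If it also leaves open which outcomes are compared, the most informative variable, baseline alcohol use, may or may not be in it.

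A mixed model fitted by likelihood uses partial follow-up and is valid if missingness is explained by observed data. The plan neither states that assumption nor tests what happens if it fails.

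**Working it through.** **1. Size of the loss (SAP 9.0).** 450 − 300 = 150; 150/450 = 33.3%. In reverse, 300/(1 − 1/3) = 450, so the plan's figures agree with each other.

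**2. The named test.** On two simulated independent groups of 225 and 224, the signed-rank test cannot be computed, because there are no pairs. The rank-sum test runs.

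**3. Can a check that ignores arm miss differential loss?** Inputs: 450 participants, assumed 1:1 (225 per arm; the ratio is not stated); 75 lost per arm (assumed equal); 30.8% users at baseline (past-year alcohol use in the earlier cohort, Protocol C, borrowed for illustration). Users per arm: 225 × 0.308 = 69.3. The loss patterns are assumptions.

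| Users among the lost, arm A / arm B | All lost | All retained | Retained A | Retained B | OR, B vs A |
|---|---|---|---|---|---|
| 30% / 30% | 30.0% | 31.2% | 31.2% | 31.2% | 1.0 |
| 40% / 20% | 30.0% | 31.2% | 26.2% | 36.2% | 1.6 |
| 45% / 15% | 30.0% | 31.2% | 23.7% | 38.7% | 2.0 |

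Second row in full: A loses 30 users and keeps 39.3 of 150 = 26.2%; B loses 15 and keeps 54.3 of 150 = 36.2%. All lost: 45/150 = 30.0%. All retained: 93.6/300 = 31.2%. OR = (0.362/0.638)/(0.262/0.738) = 1.6.

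The comparison that ignores arm sees a difference of 1.2 points with standard error √(0.30 × 0.70/150 + 0.312 × 0.688/300) = 4.6 points, so z ≈ 0.26, in all three rows.

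The arm-by-use term does respond. In the second row the odds ratio of use, lost versus retained, is (30/45)/(39.3/110.7) = 1.88 in A and (15/60)/(54.3/95.7) = 0.44 in B. Their ratio is 4.26, with log 1.45. The standard error, from the eight cell counts, is √(1/30 + 1/45 + 1/39.3 + 1/110.7 + 1/15 + 1/60 + 1/54.3 + 1/95.7) = 0.45, so z ≈ 3.2.

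Counts by arm alone would show 75 lost in each and reveal nothing.

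**4. Illustration of loss that is not at random.** Assume a binary outcome, 30% observed use in both arms, one third missing in each, and only the missing intervention participants at higher odds of use.
- Odds × 1.5: 0.4286 × 1.5 = 0.643, probability 0.391; total 2/3 × 0.30 + 1/3 × 0.391 = 0.330; OR against 0.30 = 1.15.
- Odds × 2: 0.857, probability 0.462; total 0.354; OR = 1.28.

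The inverses are 0.87 and 0.78. With 150 per arm at 30%, SE(log OR) = √(2/(150 × 0.3 × 0.7)) = 0.25, and ln(1.28)/0.25 ≈ 1.0.

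**The case against.** Several stronger readings are tempting and should be resisted.

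- *The lost have no outcomes to compare.* A reader might infer this, but substance use is measured in everyone at baseline, the primary model starts at baseline, and because attrition falls at both visits some of those lost will have 6-month data. What stands is that the outcomes are undefined.
- *The check pools the arms.* The text does not say so. It is silent on arm, which is a missing specification and not a stated wrong method.
- *Attrition is never examined, or this is the only safeguard.* Demographics are compared for everyone, SAP 4.0 adds further comparisons and counts, the model adjusts for baseline characteristics, and the protocol plans reminders, telephone contact and wide follow-up windows.
- *Only loss that differs by arm can bias the result.* Outcome-dependent loss that is the same in both arms can leave an odds ratio unbiased and still distort a difference in means. The Brief Frequency outcome is not stated to be binary.

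Two limits on the calculations also stand. The table concerns baseline use; if retention depended on nothing more, a model containing baseline use would absorb much of the imbalance. It shows what the check can miss and does not measure bias in the treatment effect. In step 4, an odds ratio of 0.78 to 0.87 would not reach significance with 150 per arm, and the plan is built around an odds ratio of 2.0, so the illustration overturns no positive conclusion. It also gives no credit for baseline or 6-month data.

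Finally, the misnamed test would surface as soon as it was programmed. Standardised differences in place of p-values for baseline balance are a reporting preference.

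**Conclusion.** The point holds in two parts. The signed-rank test is wrong for independent arms in both documents and uncorrected by any update; this is minor, because only the descriptive comparison of continuous baseline characteristics uses it. The attrition check is under-specified for an expected non-completion of 33.3%: it does not define its outcomes, plans no comparison by arm, and is not backed by any analysis that departs from missing at random. Under the assumed patterns, baseline use in the retained arms could differ by an odds ratio of 1.6 to 2.0 while lost and retained participants look alike overall.

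The conclusion rests on the documents' silence about arm and missing data, and on assumed 1:1 allocation, equal losses and the borrowed 30.8%. The odds ratio of 1.15 to 1.28 is an illustration for an assumed binary outcome at 30% and no more. Nothing in the documents shows that differential loss will occur.

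**What to change.** 1. In SAP 5.0 and Protocol H, replace the signed-rank test by the Wilcoxon rank-sum test.
2. State that the attrition check uses baseline values. Fit a model for retention on baseline past 3-month alcohol use, marijuana use, age, gender and clinic, with arm and arm-by-characteristic terms.
3. Add one sensitivity analysis of the primary alcohol outcome: multiple imputation from baseline and any 6-month data, with an arm-specific shift for missing values on the scale of the Brief Frequency outcome (an odds shift if it is analysed as binary). Report the shift at which the conclusion changes.

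The cost is some SAP wording and a small amount of extra analysis on variables already collected. Sample size, power and alpha are unchanged.
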